### Hypothesis and research questions

We hypothesise that early detection of COPD and confrontation with spirometry for smoking cessation may be effective if the following approach we have termed "confrontational counselling" is applied [20]. Confronting patients with COPD is not an isolated approach but should be integrated into state-of-the-art smoking cessation treatment. Confrontational counselling should consist of several counselling sessions on an individual, face-to-face level, under supervision of a trained smoking cessation specialist, and in combination with evidence-based pharmacological treatment for smoking cessation.

Our primary research question is: what is the efficacy of confrontational counselling in comparison to regular health education and promotion for smoking cessation delivered by specialized respiratory nurses in current smokers with previously undiagnosed mild to moderate airflow limitation (i.e. GOLD [1] stage 1 and 2 COPD) with regard to prolonged abstinence from smoking during a period of 12 months?

In this group of smokers with previously undiagnosed mild to moderate airflow limitation we want to address the following secondary research questions:

1. Which baseline characteristics are predictors of outcome (i.e. 12-month prolonged abstinence from smoking)?

2. What are the effects of early detection of airflow limitation and smoking cessation on lung function, perceived specific health-related complaints, quality of life, and mental health after 12 months follow-up?

3. What is the cost-effectiveness and cost-utility of early detection in combination with confrontational counselling delivered by respiratory nurses?

4. What are the effects of labelling of disease (COPD) on self-efficacy, perceived health status, quality of life and mental health?

5. What are the ethical considerations of early detection of airflow limitation and subsequent confrontational counselling for smoking cessation?

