### Experimental group and control group 1: L-MIS as the common basis of counselling

Participants from both the experimental group and control group 1 receive counselling delivered by a RN combined with nortriptyline for smoking cessation. The common basis for the counselling is the so-called "L-MIS" protocol for the treatment of nicotine and tobacco addiction which has been implemented among all RNs in the Netherlands in recent years [28].

The number of counselling sessions, their duration and scheduling is fixed in both the experimental group and control group 1 (see also figure 1). The first face-to-face counselling session (FC1; day 1, duration 40 minutes) starts with getting acquainted with each other. The RN tries to build up a relationship with the participant which is based on trust. The participant's smoking characteristics are defined by asking about smoking status, cigarettes smoked per day, and readiness to quit. Nicotine addiction is assessed by number of cigarettes per day and moment of smoking the first cigarette after waking up in the morning. The motivation for quitting smoking is assessed and increased by asking the readiness for quitting and reasons for smoking and quitting. Also, the health risks of smoking are discussed and the pros of quitting. The use of nortriptyline for smoking cessation is discussed, including mechanism, dosage, administration, and possible side effects (for more information about the study medication see paragraph "use of nortriptyline for smoking cessation"). The participant starts with the intake of the study medication the same day.

At the beginning of the second face-to-face counselling session (FC2; day 8, duration 40 minutes), the use of the study medication is evaluated and possible side effects are discussed. Barriers of quitting and the most important problems with previous quit attempts are discussed. The RN tries to increase the participant's self-efficacy towards smoking cessation. The focus of the second session is to prepare the participant for the target quite day (TQD). The RN discusses with the participant how to deal with the most important barriers of quitting smoking. The RN anticipates problems with withdrawal, difficult moments, and craving. The RN provides pointers for the TQD and schedules the telephone counselling on that day.

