### Follow-up visits

Three follow-up visits for all participants are scheduled at day 50 (approximately five weeks after the TQD), day 197 (approximately six months after the TQD), and day 379 (approximately twelve months after the TQD; see also figure 1). The TQD in participants from control group 2 is set at 8 weeks after the day participants were randomized and informed about group allocation. We estimated that this would be sufficient time to schedule a consultation with the GP and to prepare stopping smoking, and that the time lag between day of randomization and TQD would be about the same compared to the experimental group and control group 1 (in the latter groups, we account for a delay between day of randomization and start of treatment). Participants receive a reminder letter including a follow-up questionnaire and a cost-diary seven weeks prior to all three visits. The RA calls every participant one week prior to the visit to confirm the appointment. Minor deviations from the scheduling of follow-up visits will be allowed in order to retain as many participants in the study as possible.

At every follow-up visit, participants hand in their questionnaire and cost-diary. The RA briefly discusses the quit attempt. Urine is collected from every self-reported non-smoker for the analysis of cotinine levels.

During the final follow-up visit, spirometry is repeated in all participants. All spirometric outputs are carefully evaluated by a pulmonologist (GW) and reported to the participant's GP by letter. All participants are asked to consult their GP for information about their lung function and further treatment.

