### Data collection

An overview of all measurements per visit is given in table 1. The paper-and-pencil questionnaires are filled out at home by the participants and are handed in during the visits. Completion of the questionnaires takes about 30 minutes. Data from the questionnaires will be double-entered and checked by blinded assistants from the centre for data and information management of Maastricht University (MEMIC).

**Table 1 T1:** Overview of measurements per visit

**Measurement**	**Baseline visit**	**Follow-up visit 1 (day 50)**	**Follow-up visit 2 (day 197)**	**Follow-up visit 3 (day 379)**
Demographic characteristics	•			
Smoking:				
Tobacco use and quit attempts [41]	•	•	•	•
Fagerström Test for Nicotine Dependence (FTND) [42]	•			
Health perception: (self-constructed questions)				
health concerns	•	•	•	•
risk perception	•	•	•	•
self-exempting beliefs	•	•	•	•
Respiratory health complaints:				
COPD diagnostic questionnaire [43, 44]	•			
Medical Research Council (MRC) dyspnoea scale [45, 46]	•		•	•
Clinical COPD Questionnaire (CCQ) [47, 48]	•	•	•	•
Health-related quality of life:				
EuroQol (EQ-5D) [39, 40]	•	•	•	•
Short-form 36-item questionnaire (SF-36) [49, 50]	•	•	•	•
Chronic Respiratory Questionnaire self-reported (CRQ-SR) [51, 52]	•	•	•	•
Mental health:				
Beck Depression Inventory (BDI) [53]	•	•	•	•
Hospital Anxiety and Depression Scale (HADS) [54–56]	•	•	•	•
Cost diary: measurement of direct en indirect medical and non-medical costs [38]		•	•	•
Physical measurements:				
Physical height and weight	•	•	•	•
Post-bronchodilator spirometry	•			•
Urine cotinine (only in self-reported quitters)		•	•	•

Urine is collected from every self-reported non-smoker during each follow-up visit to validate non-smoking. The urine is kept in a 100 mL plastic cup with a screw cap and temporarily stored in a refrigerator for a maximum of seven days before delivery to the laboratory of the Department of Health Risk Analysis and Toxicology (GRAT) of Maastricht University. The concentration of cotinine in urine is measured by a highly specific radioimmunoassay using monoclonal antibodies [36]. The reagents for the assay are obtained from the Department of Biochemistry, Brandeis University, Massachusetts, USA.

The analysts assessing the urine cotinine levels and all assistants entering data from questionnaires are kept blind to the group allocation of participants.

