3. The cost-effectiveness and cost-utility of early detection of airflow limitation in combination with smoking cessation will be analysed using data from the cost diaries [38]. Participants fill out these diaries during three periods of six weeks each: during the intervention until the first follow-up visit (day 50), during the period until the second follow-up visit (day 197), and during the period until the last follow-up visit (day 379). The economic evaluation is based on direct medical costs (e.g. treatment costs, spirometry), direct non-medical costs (e.g. reimbursement of travelling expenses), and on indirect costs (e.g. sickness absence), which are related to respiratory complaints. Effects are measured in physical units (such as number of successful quit attempts, FEV_1_) and Quality Adjusted Life Years (QALY'S) are measured with the EuroQol (EQ-5D) [39,40].

4. The effects of labelling of disease (COPD) will be analysed by mediation and moderation analyses using linear and logistic regression models. The outcome variable in these analyses is abstinence from smoking at the first follow-up visit. Only data from the experimental group and control group 1 will be used.

5. The ethical considerations of early detection of airflow limitation will be analysed in a qualitative analysis using data from the ethical exit interviews which are performed in participants attending the last follow-up visit.

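### The stated analysis of secondary question 4 takes abstinence at day 50 as its outcome, although the question asks about effects of COPD labelling on self-efficacy, health status, quality of life and mental health

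*Protocol article*

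**What the plan says.** Protocol article, Hypothesis and research questions, secondary question 4: "What are the effects of labelling of disease (COPD) on self-efficacy, perceived health status, quality of life and mental health". Labelling is the exposure, and the four domains are what it may affect.

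Protocol article, Data analysis, item 4 of the list that takes the secondary questions in order: "The effects of labelling of disease (COPD) will be analysed by mediation and moderation analyses using linear and logistic regression models". It continues: "The outcome variable in these analyses is abstinence from smoking at the first follow-up visit". The data are restricted: "Only data from the experimental group and control group 1 will be used". Neither the mediators nor the moderators are named.

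Protocol article, Data collection: "An overview of all measurements per visit is given in table 1". Table 1 lists CCQ, EQ-5D, SF-36, CRQ-SR, BDI and HADS at baseline and at days 50, 197 and 379. The block headed "Health perception: (self-constructed questions") covers health concerns, risk perception and self-exempting beliefs. No row is for self-efficacy. Outside the research question, the term appears only as an aim of the second counselling session: "The RN tries to increase the participant's self-efficacy towards smoking cessation".

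**The concern.** The question and its analysis point in different directions. The question puts health status, quality of life and mental health on the outcome side. The analysis puts abstinence there, which the question does not mention.

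At stake is the estimate of possible harm. The section on confrontational counselling acknowledges that telling someone about a serious disease arouses fear, and the Conclusion says that a positive effect on cessation would argue for early detection. A reader weighing that argument needs to know what the confrontation does to anxiety, depression and quality of life. Question 4 is where the protocol promises this, and the trial collects the scales for it. If the analysis is carried out as written, the main reported result for question 4 will be about smoking.

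A second issue is temporal order. If questionnaire measures from the first follow-up serve as mediators, they belong to the same visit as the abstinence outcome, and having quit may already have changed them.

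**Working it through.** No figure needs recomputing; the check compares the article's sections.

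**1. Question against analysis.** The Data analysis section numbers its items by research question, so the mismatch is not one of numbering.

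| Domain in question 4 | Named as outcome in item 4 | Instrument listed in Table 1 |
|---|---|---|
| Self-efficacy | no | none |
| Perceived health status | no | CCQ, SF-36, EQ-5D |
| Quality of life | no | SF-36, EQ-5D, CRQ-SR |
| Mental health | no | BDI, HADS |

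None of the four is named as an outcome. Three have instruments at all four visits; one has none listed. (The assignment of scales to perceived health status is my reading; the table groups them slightly differently.)

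**2. Does another analysis fill the gap?**
- Question 1 predicts abstinence from baseline variables. It does not.
- Question 2 asks about the effects of early detection as well as cessation, but its analysis regresses the health measures on abstinence only. Abstinence arises after randomisation and is not itself randomised, so this is not a comparison by group.
- Question 3 derives QALYs from the EQ-5D for a cost-utility analysis. That implies a group contrast on this one instrument, although no comparator is named. It covers neither mental health scale, nor the CCQ or CRQ-SR.
- Question 5 is qualitative.

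So no comparison by randomised group is explicitly stated for BDI, HADS, CCQ, CRQ-SR or SF-36.

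**3. Order of mediator and outcome.** On the visits the article says: "Three follow-up visits for all participants are scheduled at day 50 (approximately five weeks after the TQD"). In the two nurse-led groups the target quit date is day 14, so abstinence at day 50 reflects behaviour over about 50 − 14 = 36 days. The follow-up questionnaire is sent seven weeks (49 days) before each visit and completed at home. For the first visit that is about day 50 − 49 = day 1. A participant could therefore complete it at any point between roughly day 1 and day 50, before or after quitting. The plan does not fix the order. Abstinence at days 197 and 379 would come after the day-50 questionnaire.

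**4. What the group contrast identifies.** The experimental group differs from control group 1 in more than the label. It also receives cognitive-therapy techniques, a different counselling style and homework diaries, from separate nurses who are additionally trained and supervised. A comparison of the two groups estimates the effect of that package. It is still the contrast that item 4 itself selects.

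**The case against.** The strongest reply is that a mediation analysis has two parts. Abstinence is binary and takes the logistic model. The linear models that item 4 also mentions would naturally regress continuous mediators on group, and if quality of life or mental health were among those mediators, the group effect on them would be estimated along the way. This stands in part. A reader might infer that the planned analysis cannot answer question 4 at all, and the article does not support that. But it names no such mediators, and an unnamed intermediate step is not a commitment to report the effects that the question asks for.

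Three other strong readings also go further than the text:
- *That no randomised comparison of quality of life is planned anywhere.* The EQ-5D cost-utility analysis implies one.
- *That self-efficacy is never measured.* Table 1 is not exhaustive: it omits the interview on GP care, the pill count and the exit interviews, all described elsewhere. An item inside a listed questionnaire cannot be ruled out either. What can be said is that no self-efficacy measure is listed in the table or elsewhere in the article.
- *That mediator and outcome are measured at the same moment.* Neither the mediators nor their timing is stated, and moderators could be baseline values. The caution about order is conditional on day-50 questionnaire measures being the mediators.

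It could also be said that a condensed article leaves model details to an analysis plan. That covers the choice of mediators, but not an outcome variable that the article states and that differs from those in its own question.

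**Conclusion.** The concern holds for the outcome named in item 4. As written, the stated analysis does not target question 4: none of its four domains is named as an outcome, and no self-efficacy measure is listed. No comparison by randomised group is explicitly stated for anxiety, depression or disease-specific quality of life.

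Severity is moderate. This is one of five secondary questions; the primary comparison, its sample size and its test are unaffected. The data for health status, quality of life and mental health are already scheduled at every visit, with 150 participants planned in each of the two groups, so the estimates can be obtained without new data. They would describe the whole confrontational counselling package, which limits what can be concluded about labelling alone.

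The verdict assumes that the article states the question 4 outcome as intended and that no fuller document assigns other outcomes to it.

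**What to change.** 1. For question 4, name SF-36, EQ-5D, CCQ, CRQ-SR, BDI and HADS at days 50, 197 and 379 as the dependent variables. Compare the experimental group with control group 1 as randomised, adjusting each scale for its baseline value, by analysis of covariance or one repeated-measures model per scale.
2. State that this contrast reflects the whole confrontational counselling package, not labelling alone.
3. Name the self-efficacy measure and the visits at which it is taken, or delete self-efficacy from the question. A newly added scale would lack a baseline value for anyone already enrolled, in which case deletion is cleaner.
4. Keep mediation and moderation as a separate exploratory analysis and name the mediators. If these are day-50 questionnaire measures, use abstinence at day 197 or 379 as the outcome.

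Rewording question 4 as a mediation question about abstinence would also remove the contradiction, but it would give up the stated interest in the effects on health and mood.

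The cost is one rewritten analysis paragraph and either one word deleted or at most one short scale added to an existing questionnaire.

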### Ethical approval, review, and registration of the trial

Participants of this study are not fully informed about the real purpose of the study at the beginning, which is to detect and confront smokers with airflow limitation. Participants from control group 1 and control group 2 are not informed about their results of spirometry during the intervention and follow-up period. This approach is necessary to assess the additional effect of early detection of and confrontation with airflow limitation above the effects of individual counselling and medication use. As already explained in the paragraph "informed consent", all participants as well as their GPs will be fully informed about the purpose of the study and the results of spirometry after the last follow-up visit.

This procedure is approved by the medical ethics committee of Maastricht University and Maastricht University Hospital. We believe that it is ethical to withhold information about the results from spirometry to participants of this study for at least two reasons. The first reason is that the smokers participating in this trial would probably not have been diagnosed with airflow limitation outside the trial setting early due to the problem of underdiagnosis of COPD in primary care. The second reason is that all smokers from this trial receive the most effective therapy for airflow limitation from either the RN or their own GP, which is smoking cessation treatment.

Data from the ethical analysis, which is based on the interviews with participants during the last follow-up visit, should provide information about the participants' view on the ethical aspects of this trial.

The protocol of this study was extensively reviewed by the funding organizations; the Dutch Asthma Foundation, PICASSO for COPD, and Maastricht University Hospital. The study is registered at the Netherlands Trial Register (ISRCTN 64481813).

### Time frame

The recruitment, inclusion, randomization, and treatment of participants will start in 2005 and will continue until 2007. The follow-up of participants is planned until the year 2008. All data will be continuously collected, entered, and cleaned. The analysis of data regarding the primary research question will not be initiated before the completion of follow-up and data collection in the last participants (during the course of the year 2008).

## Discussion

We presented the protocol of a study assessing the efficacy of confrontational counselling for smoking cessation in current smokers with not earlier diagnosed mild to moderate airflow limitation (i.e. GOLD stage 1 and 2 COPD). The design of this study is a randomized controlled trial comparing confrontational counselling delivered by a respiratory nurse (RN) combined with nortriptyline for smoking cessation (experimental group), health education and promotion delivered by a RN combined with nortriptyline for smoking cessation (control group 1), and "care as usual" delivered by the GP (control group 2). We hypothesise that early detection of COPD and confrontation with spirometry for smoking cessation is more effective than regular health education and promotion and primary care as usual for smoking cessation.

In the design of this randomized controlled trial, the baseline risk of all participants is the same; they all have previously undetected airflow limitation. Only participants from the experimental group are confronted with their disease. Participants from the two control groups are not informed before the end of the trial. All other factors which are known to be associated with abstinence from smoking are standardised in both the experimental group and control group 1: type of counsellor (RN), type of counselling (face-to-face and by telephone), number and duration of counselling sessions, and type (nortriptyline) and dosage of smoking cessation medication. Therefore, we are able to assess the "net" effect of confronting and counselling smokers with COPD.

There are several critical success factors to be mentioned. A large number of smokers will have to be screened in order to obtain enough eligible participants. No smokers with known airflow limitation are allowed to enter the trial. Also, during the whole recruitment period, candidate participants must not be informed about the real purpose of the study at the beginning; to detect and confront smokers with airflow limitation. This means that a large number of smokers generally interested in quitting must be recruited in order to filter out eligible smokers with airflow limitation.

We expect eligible smokers to have a strong preference to be placed in one of the groups receiving counselling by a RN in combination with smoking cessation medication, because they may find this intervention more effective than care as usual by their own GP. Therefore, we expect a lower compliance in participants from control group 2 and differential lost to follow-up in this group. It should be noted here that the intervention in control group 2 is probably not care as usual for smoking cessation as it appears in primary care. This is because smokers are more or less "referred" from the study team to their GP and are likely to ask for the same smoking cessation medication as participants randomized to the other two groups (nortriptyline).

Blinding of neither participants nor RNs is possible, because we want to assess behavioural interventions. All participants know what kind of counselling they receive, as do the respiratory nurses who provide the counselling. However, analysts assessing the cotinine levels and assistants entering data from questionnaires are blinded for the group allocation of participants.

The primary outcome, 12-month prolonged abstinence from smoking, is estimated from abstinence measures at three time points. This outcome is therefore no perfect measure of continuous outcome, but it is a feasible estimation, which is very usual in this field of research. Abstinence from smoking is the primary endpoint of this study, but can be regarded as a surrogate for the expected long-term positive effects of smoking cessation on health.

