### Sample size calculation

The primary research question aims at a contrast in efficacy between the experimental group (confrontational counselling) and control group 1 (health education and promotion). Therefore, the calculation of the sample size is based on the identification of a difference in proportion of prolonged abstinence after 12 months between these two groups. We estimated the relevant difference in proportion to be 15%: 35% quitters in the experimental group versus 20% quitters in control group 1. When putting the risk of a type I-error at 5% and the risk of a type II-error at 20%, 136 participants per group are needed at onset to detect a difference in proportions of 15%. Considering 10% lost to follow-up, 150 participants per group are needed in the experimental group and control group 1 (136 × 0.9^-1^). We expect a larger difference between the experimental group (35%) and control group 2 (8% [22]). Therefore, less participants are needed in control group 2. We used a formula for the calculation of sample sizes of unequal groups and set the ratio between the experimental group and control group 2 at 3:1. This resulted in a minimum of 32 participants in control group 2 (taking into account 10% lost to follow-up).

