### Control group 2: care as usual by GP

Participants from control group 2 are referred to their own GP for smoking cessation treatment. They are asked to make an appointment with their GP within the next ten days. They are provided with a referral letter explaining to the GP that the person is participating in a study on smoking cessation. This letter does not give any information about the results from spirometry and the fact that the participant has airflow limitation. The GP is asked to provide the care he/she usually provides to patients who want to quit smoking. In the Netherlands, primary "care as usual" for smoking cessation involves the use of a protocol for low intensity health education and promotion, the so-called "H-MIS" [22]. According to the protocol of the H-MIS, the GP and/or the assistant takes the following steps to assist the smoker during a quit attempt: determine the smoking profile of the smoker, determine the motivation to stop smoking (and increase the motivation if necessary), talk about the barriers of quitting smoking, set a target quit date, discuss the use of smoking cessation aids, and arrange follow-up. A semi-structured interview will be used among participants from control group 2 during the first follow-up visit (day 50) in order to assess whether participants have consulted their GP and which treatment for smoking cessation the GP has delivered.

Neither participants from control group 2 nor their GP will be informed about the results from spirometry and the detected airflow limitation. However, if a GP explicitly requests the results from spirometry they will be provided (see further paragraph "ethical considerations").

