## Conclusion

Early intervention in COPD is of paramount importance because of the irreversible and progressive nature of the disease. The use of spirometry for early detection of COPD still is an issue of debate because of a lack of convincing evidence that spirometry has an added positive effect on smoking cessation. A significant and relevant effect of confrontational counselling compared to regular health education and promotion for smoking cessation would provide an argument in favour of early detection of current smokers with airflow limitation. Successful treatment of tobacco dependence in respiratory patients requires repeated intensive interventions. The results of this study may show that RNs are able to deliver this treatment on the and that intensive smoking cessation counselling is more feasible for RNs than for physicians who often lack time.

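### Against control group 2 the trial can test the whole nurse-led package, not detection and confrontation, and it cannot compare feasibility between nurses and physicians

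*Protocol article*

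**What the plan says.** The primary research question and the sample size concern the experimental group v control group 1, with "35% quitters in the experimental group versus 20% quitters in control group 1". For control group 2 the plan assumes 8% and sizes the group at a minimum of 32.

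The opening paragraph of the Discussion goes further. It hypothesises that early detection and "confrontation with spirometry for smoking cessation is more effective than regular health education and promotion and primary care as usual for smoking cessation".

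Control group 2 is described under its own heading in Methods: "The GP is asked to provide the care he/she usually provides to patients who want to quit smoking". Later in the Discussion the article concedes that "the intervention in control group 2 is probably not care as usual for smoking cessation as it appears in primary care". It also expects lower compliance and differential loss to follow-up in that group.

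The Conclusion says the results may show that nurses can deliver the treatment and that "intensive smoking cessation counselling is more feasible for RNs than for physicians who often lack time".

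**The concern.** The care-as-usual half of the hypothesis names two causes, detection and confrontation. Neither is isolated by comparing the experimental group with control group 2. Detection does not vary at all, and confrontation varies together with several other things that affect quitting. The Study design section sets the relevant rule itself: to isolate the effect of confrontational counselling, other factors associated with the outcome have to be standardised between the groups compared. The Discussion claims that standardisation only for the experimental group and control group 1.

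A significant difference from control group 2 could then be reported as confirming this hypothesis, although part of it would come from nurse counselling with nortriptyline that does not mention spirometry. Because absent participants count as smokers, the differential loss that the article expects would also lower the abstinence rate in control group 2 directly.

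The feasibility remark in the Conclusion is a separate problem. It is a comparison between professions for which the trial has no comparison.

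**Working it through.** **What differs between the groups** (from Study design, eligibility screening, the group descriptions, Use of nortriptyline, Follow-up visits and Discussion)

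| Factor | Experimental | Control group 1 | Control group 2 |
|---|---|---|---|
| Airflow limitation detected before randomisation | yes | yes | yes |
| Result disclosed and used in counselling | yes | no | no (GP told only on request) |
| Counsellor | respiratory nurse | respiratory nurse | own GP |
| Counselling | four 40-minute sessions and a call | same | GP's usual care; low-intensity H-MIS |
| Nortriptyline | by protocol | by protocol | not set by protocol; patients may ask for it |
| Target quit date | day 14 of programme | same | 8 weeks after randomisation |

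The experimental group and control group 1 differ in the confrontational component. The experimental group and control group 2 differ in every row but the first, with medication possibly overlapping.

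**The plan's own sample sizes**

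- 35% v 20%, two-sided 5% (sidedness assumed), power 80%, unpooled normal formula: (1.960 + 0.842)² × (0.35×0.65 + 0.20×0.80) / 0.15² = 135.2, so 136 per group. Allowing for loss, 135.2/0.9 = 150.2, in line with the stated 150.
- 35% v 8%, continuity-corrected: 43 per group if equal. At 3:1 the smaller group is 43 × 4/6 = 28.7, and 28.7/0.9 = 31.9, so 32 as stated.

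The planning rates are therefore read as the plan uses them.

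**How much of the gap to control group 2 is expected without confrontation**

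- Experimental minus control group 2: 35 − 8 = 27 points.
- Control group 1 minus control group 2: 20 − 8 = 12 points, and 12/27 = 44%.
- Experimental minus control group 1: 35 − 20 = 15 points, and 15/27 = 56%.

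**What a significant result against control group 2 would mean if confrontation had no effect**

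Set the experimental group to 20%, equal to control group 1, and keep control group 2 at 8%. The chance of significance in favour of the experimental group is Φ[(d − 1.96·SE₀)/SE₁], with d = 0.12, SE₀ pooled and SE₁ unpooled.

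- 150 v 50 (150:150:50, from the 3:3:1 allocation). Pooled rate (30 + 4)/200 = 0.17. SE₀ = √[0.17×0.83×(1/150 + 1/50)] = 0.0613. SE₁ = √[0.16/150 + 0.0736/50] = 0.0504. Result: Φ[(0.12 − 0.1202)/0.0504] = 0.50.
- 150 v 32 (the stated minimum). Pooled rate (30 + 2.56)/182 = 0.179. SE₀ = 0.0746, SE₁ = 0.0580. Result: Φ[(0.12 − 0.1463)/0.0580] = 0.33.

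Exact enumeration of the uncorrected test gives about 0.51 and 0.35.

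At the full planning rates (35% v 8%, 150 v 50) the same formula gives 0.99. A significant result against control group 2 is thus only about twice as likely (0.99/0.50) when confrontation works as planned as when it does nothing.

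**Feasibility by profession**

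GPs in control group 2 are asked only for their usual care. The research questions, Table 1 and the Data analysis section contain no measure or analysis of feasibility for physicians, or of nurses against physicians.

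**The case against.** The best defence is that the article ties its causal claim to control group 1. The primary question, the sample size and the claim of a net effect all concern that contrast. The Conclusion bases the case for early detection on an effect against health education alone. This stands: the primary contrast is unaffected, and so is the control group 1 half of the hypothesis.

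A second defence is that the article defines confrontational counselling as part of a full programme of sessions and drug treatment, so the hypothesis can be read as a claim about the package. This also largely stands. A reader might infer that control group 2 supports no conclusion at all, but the documents do not bear that out. Randomised experimental v control group 2 can support superiority of the whole nurse-led package over referral to the GP. The wording in the Discussion, however, credits detection and confrontation rather than the package.

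Third, medication need not differ. The H-MIS includes discussing cessation aids, and the article expects control group 2 participants to ask for nortriptyline. It is right to call medication unstandardised rather than certainly different. The article also plans an interview at day 50 on what the GP delivered, and it discloses the weakness of control group 2 itself. Those caveats are absent from the hypothesis.

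Fourth, a reader might infer that the feasibility remark rests on control group 2 and is confounded. The Conclusion does not invoke that group, and it hedges with the word may. The abstract's version does not mention physicians. The flaw in the Conclusion is a missing comparison, and hedging does not supply one.

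Finally, the 44%/56% split subtracts planning assumptions and is no forecast. The three-group design already allows the two parts to be shown separately.

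**Conclusion.** The point holds in a limited form. As worded, the care-as-usual half of the hypothesis assigns to detection and confrontation a difference that also reflects counsellor, counselling intensity and protocol v unstandardised medication. The comparator is one that the article itself doubts is care as usual.

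On the planning rates, 12 of 27 points (44%) would arise without confrontation. With no confrontation effect, the comparison would still be significant with probability about 0.50 at 150 v 50, or 0.33 at 150 v 32. These figures assume that the 20% and 8% rates hold, that the test is two-sided at 5%, and that the experimental and control group 1 rates would be equal without confrontation.

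Separately, the nurse-v-physician feasibility suggestion cannot be tested in this trial, whatever the data show. The narrower statement that nurses can deliver the programme can be informed by the two nurse-led groups.

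Neither matter changes the sample size, the outcome or the primary analysis. They change what the trial may conclude.

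**What to change.** - Word the control group 2 hypothesis as the nurse-led package of confrontational counselling plus nortriptyline v study referral to the GP.
- Tie any effect of confrontation to experimental v control group 1 only.
- Whenever experimental v control group 2 is reported, show control group 1 v control group 2 beside it, as differences with confidence intervals. At the planning rates (20% v 8%, 150 v 50) a test of the latter has power of only about 0.50, so a non-significant result should not be read as no effect of nurse counselling with nortriptyline.
- Drop the nurse-v-physician comparison from the Conclusion. Limit the statement to whether nurses can deliver the programme, using the intervention registration forms they already complete at each session.

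The cost is a few sentences and one extra contrast from data already collected, with no change to conduct or sample size. The downside is a more modest claim.
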